A qualitative study developed with patients with HCV who inject drugs revealed the difficulties to access to HCV treatment and highlighted the need for nurse navigator services that help patients navigate through a complex and fragmented healthcare system [33]. Moreover, some experiences with SMD patients with physical comorbidities treated in the US Medicaid system based on a nurse-navigator model have shown promising results in the seamless management of mental and physical health problems [34]. However, for these services to be effective, a solid and consistent approach is required, with well-defined limits and sufficient resolution capacity to bridge the various gaps that arise throughout the process [35]. Ryvicker's [36] behavioral-ecological conceptual framework for navigation addresses these two requirements. Thus, individual predisposing and limiting factors determine the degree to which a patient is able to navigate effectively through the health system (educational level, health literacy, communication skills, degree of self-efficacy, support from family caregivers, among others). The complex interaction between predisposing, facilitating, limiting factors and patient’s needs end up shaping their lifestyles and health practices. Provider factors such as continuity of care from different healthcare professionals, communication or respect and trust towards patients must also be considered. The confluence of these factors influences health outcomes, generating exacerbations of chronic diseases, hospitalizations, changes in functional status or poor quality of life. Finally, this model establishes ecological determinants such as the environment of health services, the social context of the person and the environment of people's lives. In the case of people with SMD both, predisposing and limiting behavioural factors, as well as ecological ones, acquire special relevance. Thus, when a SMD patient is diagnosed with a physical illness and treatment instructions are provided to them, patients will frequently not start the treatment immediately; instead, they will probably wait to discuss it first with their psychiatrist or mental health nurse or go home and not discuss the matter ever again. There are barriers during the consultation process, follow-up, and ongoing care, both associated to the health care providers and the patient that may lead to a poor compliance with a non-psychiatric treatment [37].

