## The study

### Aims

The objective of this study is to compare the effectiveness of a nurse navigator program (NNP) developed by a team of mental health nurses, aimed at patients with HCV and SMD versus the usual standard of care. The variables to be assessed include HCV testing, treatment access and adherence, support for navigation throughout the healthcare system, and recovery from HCV.

The null hypothesis of this study is that there will be no differences in the HCV cure rate in SMD subjects who engage in the NNP versus those who receive the standard of care. Additionally, a second hypothesis would be that the intervention improves adherence to HCV treatment, expressed as a percentage based on the taken doses of prescribed treatment during the treatment period (from 0% to ≥ 100%).

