##### Endpoints and measures

The cure rate and adherence to treatment will be the primary endpoints. To assess cure, HCV viral load will be determined 8–12 weeks after the end of treatment. Patient adherence to treatment will be evaluated using the AIDS Clinical Trials Group method. By this method, patients are inquired about medications not taken in a period of four days prior to the interview: % adherence = (total galenic units prescribed for that period—total units not taken) / total galenic units prescribed for that period [40]. The cut point for this measure has been set to 95%, as the best threshold for a predictive positive virologic response in patients with HIV [41]. A record will also be kept of whether the patient needed to use a pillbox to ensure medication intake and/or required monitoring by the family or the mental health unit to guarantee the correct use of the treatment.

Secondary endpoints include sociodemographic and clinical data and data related to the healthcare process. Other variables in relation to the patient include changes in daily functioning as assessed using the Life Skill Profile (LSP) [42]; negative symptoms, measured on the Positive and Negative Syndrome Scale (PANSS) [43]; and changes in quality of life, measured with the Euroqol5D Health Questionnaire [44], all of them in their Spanish version (See Table 1). These questionnaires will be administered by an evaluator (psychologist or nurse) trained for it and blind to the experimental condition assigned to each patient.

**Table 1 Tab1:** Psychometric characteristics of the instruments included

Questionnaire	Domain (s)	Psychometric properties
**Life Skill Profile (LSP)** [42]	Self-care	Concurrent validity, this scale was compared with the social behaviour schedule SBS: 0.56 Interrater reliability *r* = 0.62, and internal consistency α = 0.82
	Interpersonal social behaviour	Concurrent validity, this scale was compared with the social behaviour schedule SBS: 0.54 Interrater reliability *r* = 0.69, and internal consistency α = 0.77
	Communication and social contact	Concurrent validity, this scale was compared with the social behaviour schedule SBS: 0.63 Interrater reliability *r* = 0.86, and internal consistency α = 0.86
	Non-personal social behaviour	Concurrent validity, this scale was compared with the social behaviour schedule SBS: 0.36 Interrater reliability *r* = 0.76, and internal consistency α = 0.78

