#### Monitoring

During the treatment period (8–12 weeks depending on the prescribed drug), actions will be taken to ensure correct treatment adherence. To such purpose, the mental health nurse will assess patient’s ability to comply with the treatment. In case of patient’s inability, the nurse will assess family’s commitment to supervise and remind the patient about drug intake. In both cases, the nurse will carry out an educational intervention to ensure that the patient and/or their family clearly understand treatment guidelines. This intervention is structured through a standardized care plan. In cases in which proper treatment use is not guaranteed, medication will be provided weekly by the monitoring team.

Upon completion of the 8–12 weeks treatment period, a final evaluation of all patients will be performed. The data collected in this evaluation visit include adherence to treatment, person responsible for treatment administration, occurrence of adverse effects or interactions, and number of visits and calls during the treatment period.

A third and final analysis of all study variables will be carried out six months after starting the treatment. Finally, disappearance of the viral load and, therefore, cure from HCV will be determined by a new blood test.

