#### Data analysis

First, an exploratory data analysis will be performed to determine the distributions of the different variables and evaluate their normality using the Kolmogorov–Smirnov test, kurtosis analysis and skewness. Measures of central tendency and dispersion will be calculated, as well as percentage distributions. Subsequently, a bivariate analysis will be performed using the Chi-square test for comparison of qualitative variables, and Student's *t*-test for independent groups for quantitative variables. In case of non-parametric distribution, the Mann–Whitney *U* test will be performed.

In addition, repeated measures ANOVA will be used to determine intra-group progression of the different variables throughout the monitoring period, to evaluate the time effect.

Finally, a multivariate regression model will be constructed using Cox regression to evaluate the primary endpoints (cure and adherence), with follow-up periods as time adjusted for the variables found to have a significant association on bivariate analysis. The raw and adjusted hazard ratio for treatment failure and non-adherence will be estimated.

All the analyses will be performed by intention to treat (ITT) and by multiple imputation using the monotonic approach if missing data show a monotonic pattern; otherwise, the fully conditional specification will be used. Patients will be analysed in the group to which they will be initially allocated, regardless of whether they finally receive the randomized intervention.

All analyses will be done with estimation of 95% confidence intervals.

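### Read literally, the plan imputes cure and adherence for randomised patients who never start treatment from patients who did, which removes the access part of the navigator's effect

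*Protocol article*

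**What the plan says.** All references are to the protocol article.

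- **Endpoints and measures** names two primary endpoints: "The cure rate and adherence to treatment will be the primary endpoints". For cure, "HCV viral load will be determined 8–12 weeks after the end of treatment". Adherence is the share of units not missed over a four-day window, divided by the "total galenic units prescribed for that period". **Aims** likewise describes adherence as "a percentage based on the taken doses of prescribed treatment during the treatment period".
- **Monitoring** counts the last assessment from treatment as well: "A third and final analysis of all study variables will be carried out six months after starting the treatment". The Abstract also times follow-up from the antiviral.
- **Interventions** separates the arms before prescription. Controls go to the family physician, then to the gastroenterologist after a delay, then for tests in other units, then back to the gastroenterologist for a prescription. Navigator patients are accompanied to one visit and leave with the drug that day.
- **Aims** makes access part of what is studied: "The variables to be assessed include HCV testing, treatment access and adherence".
- **Data analysis** states: "All the analyses will be performed by intention to treat (ITT) and by multiple imputation", by a monotone method or fully conditional specification. It keeps patients in their allocated group but does not say what outcome value a patient has if the antiviral is never started.

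**The concern.** Under Data collection and Ethics, patients enter the trial with a positive viral load. One who is never treated is not a patient with an unknown result: no dose was taken, and cure cannot be credited to treatment. But the endpoint definitions give that patient no scheduled viral load, and no adherence value if nothing was prescribed. The only tool the plan offers for an empty outcome is multiple imputation, which would draw a value from patients who were treated.

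The two kinds of non-starter differ. A patient who was prescribed the drug and took none already scores 0% adherence under the formula, but still has no post-treatment viral load. A patient never prescribed lacks both outcomes. The longer control pathway would tend to produce the second kind.

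At stake is what the trial estimates. A navigator can raise cure by getting more patients onto treatment, by improving results among those treated, or both. Imputing non-starters from starters discards the first route, although access is a stated aim.

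**Working it through.** **The plan's own figure.** The section Sample gives 276 patients for adherence of 80% vs 65%, alpha 0.05 and beta 20%. With pooled variance, a two-sided test and 1:1 allocation (sidedness and ratio are not stated), the mean proportion is 0.725 and

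n per arm = [1.96·√(2·0.725·0.275) + 0.8416·√(0.80·0.20 + 0.65·0.35)]² / 0.15² = (1.2377 + 0.5239)² / 0.0225 ≈ 137.9, so 138 per arm and 276 in total. The figure reproduces.

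**Notation.** Let s_N and s_C be the proportions starting treatment in the navigator and control arms, and c_N and c_C the success proportions among starters. Assume that no untreated patient is cured.

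- Non-starters counted as failures: difference = s_N·c_N − s_C·c_C.
- Non-starters imputed within arm from starters: difference = c_N − c_C in expectation.

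The documents give no initiation rates and no cure rate among starters. The values below are assumptions, except the pair 80% vs 65%, which is borrowed from the planned adherence rates.

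| Start (navigator / control) | Success among starters | As failures | Imputed | Share lost |
|---|---|---|---|---|
| 95% / 85% | 95% / 95% | 0.9025 − 0.8075 = 0.095 | 0 | 100% |
| 95% / 75% | 95% / 95% | 0.9025 − 0.7125 = 0.190 | 0 | 100% |
| 90% / 60% | 95% / 95% | 0.8550 − 0.5700 = 0.285 | 0 | 100% |
| 95% / 85% | 80% / 65% | 0.7600 − 0.5525 = 0.2075 | 0.15 | 0.0575/0.2075 = 28% |
| 95% / 75% | 80% / 65% | 0.7600 − 0.4875 = 0.2725 | 0.15 | 0.1225/0.2725 = 45% |
| 90% / 60% | 80% / 65% | 0.7200 − 0.3900 = 0.330 | 0.15 | 0.1800/0.330 = 55% |

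**Simulation.** 4,000 trials with 138 per arm, 20 imputations within arm from starters, combined by Rubin's rules:

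- The planned 80% vs 65% produced wholly by access (85% success among starters in both arms; initiation 0.80/0.85 = 94.1% and 0.65/0.85 = 76.5%). As failures: difference 0.150, power 80%. Imputed: difference 0.001, rejection rate 4.8%.
- Initiation 95% vs 75%, success 95% in both arms. As failures: 0.191, power 98%. Imputed: 0.001, rejection rate 5.8%.
- Initiation 95% vs 75%, success 80% vs 65%. As failures: 0.273, power 99.7%. Imputed: 0.151, power 74%.

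**Direction.** The bias runs towards no difference when controls start less often, as in all rows above. It is not automatic. With 90% starting in both arms and success of 80% vs 65%, the difference among all randomised is 0.90·0.15 = 0.135 against 0.15 imputed, a slight overstatement.

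**The case against.** The strongest reply is that the article never says non-starters are missing. Data analysis also plans hazard ratios for treatment failure and non-adherence, and failure could be meant to include an untreated viraemic patient. Outcome coding of this kind is often left to a statistical analysis plan, which is not shown. This stands in part: the classification is inferred from the treatment-timed endpoints and the single rule given, and an unseen plan could override it. But the issue is more than absent detail. The rule that is stated covers all analyses and, followed as written, gives a wrong value. Failure is not defined to include never starting.

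Three stronger readings are tempting, and the documents do not support them:

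- *Many patients will never take treatment up.* Background says that patients often delay starting. To "go home and not discuss the matter ever again" is offered there as one of two alternatives, about physical illness in general and not about consented trial patients.
- *No non-starter has an adherence value.* That is true only where nothing was prescribed.
- *The whole effect is erased.* That needs equal success among starters in both arms. If starters differ, their difference survives.

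Two further points are fair. Endpoints and measures lists referral percentage and delay to first specialist visit as process indicators, so access is not lost from the trial altogether, but these are not primary endpoints. Monitoring promises a final evaluation of all patients, but on completion of the treatment period, which gives a never-starter no date.

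**Conclusion.** The point holds as a consequence of the text read literally. It affects both primary endpoints: cure for every non-starter, adherence for those never prescribed. Imputation under missing at random replaces the comparison of all randomised patients with one among starters and removes the access component.

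The size cannot be fixed from the documents. Under the assumed initiation rates, the loss is the whole effect if starters do equally well, and about 28–55% of it if they differ 80% vs 65%. Bias towards no difference is probable rather than certain, since it rests on more control patients failing to start. The calculations assume imputation within arm from starters without further predictors, and no cure without treatment. The intention-to-treat statement does not help, because it fixes the group in which a patient is analysed and not the outcome.

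**What to change.** In Data analysis:

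1. Define the primary outcome at a fixed time counted from randomisation, long enough for the control pathway, treatment and the post-treatment test. Treatment and test alone take up to 12 + 12 = 24 weeks by the article's own ranges. The control delay, which is not quantified, comes on top.
2. Count randomised patients with no antiviral started by that time as not cured and 0% adherent.
3. Limit multiple imputation to patients who started but lack a result.
4. Add a sensitivity analysis counting every patient without a documented negative viral load as not cured.

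The cost is modest but goes beyond wording. A randomisation-based analysis date has to be added, because every present date depends on treatment. Reported cure and adherence will be lower in both arms. The change should be made before outcomes are examined by arm, since afterwards it would look data-driven.

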## Discussion

The present study addresses several health issues that have not yet been analysed in Spain. Novel drugs different from interferon with proven effectiveness and tolerability in SMD patients have been approved [47]; the scientific literature, however, still shows that this population is at an increased risk for acquiring infectious diseases such as HCV [17, 48]. There is also evidence of difficulties in detecting and treating HCV and concomitant physical comorbidities in this population [49–51]. This study will provide data on the feasibility of a NNP aimed at improving coordination between the different specialists who treat patients with SMD and physical comorbidities, in this case, HCV. Moreover, if the results show that this approach is effective, it would be applicable to many other comorbidities that are frequently found in this population and remain undiagnosed and undertreated.

Likewise, there is consistent evidence that patients with SMD often have treatment adherence problems [52, 53]. This population of patients also show difficulties in navigating through complex clinical pathways that imply attending several appointments in various health services at different times, probably due to their impaired executive function [54, 55]. In the case of HCV, the clinical pathway involves, but not limited to, visits to the services of mental health, microbiology, primary care, digestive medicine, and hospital pharmacy. When the patient has adherence problems, it may be necessary that they are accompanied throughout complex processes including follow-up visits related to physical health problems. These patients are frequently accompanied by nurses [56, 57]. For this randomized controlled trial, an approach tailored to patient’s needs and context will be adopted to maximize treatment adherence and, as far as possible, ensure resolution of HCV infection. Once the study is completed, this model of care will be offered to the rest of patients of the Mental Health Service Unit of the University Regional Hospital of Málaga. If the trial proves to be effective, this model could be easily applied at other Mental Health services. Moreover, the study is designed from a pragmatic approach, with no extraordinary modifications of daily practice, except for the implementation of an NNP. Thus, the intervention will be implemented by the Mental Health Unit staff itself. If results are satisfactory, the sustainability of the model is guaranteed and its generalization to other Mental Health Units of the Public Health Care System is easily achievable in Spain. Furthermore, mental health services are well-positioned to lead a more active role in the treatment of HCV and engage patients in the treatment process [49].

A secondary contribution of this study is that it will provide data on the prevalence of HCV symptoms such as apathy, anhedonia, tiredness (Negative symptoms scale, PANSS), which are commonly attributed to schizophrenia or to the side effects of usual pharmacological treatments such as antipsychotics or mood stabilizers. During the study, all these symptoms will be recorded at baseline and once infection has been cured. Consequently, it is a unique opportunity to assess the occurrence of symptoms once HCV infection is resolved. If these symptoms persist after HCV infection is controlled, a psychotic aetiology will be confirmed.

### Limitations

This study has several limitations. One of them is that all participants will be recruited in a single hospital; therefore, these findings will require replication in other settings to confirm consistency. Another possible limitation is that there are people with SMD and HCV infection who are not being treated in mental health services (homeless people with psychosis, people with poor accessibility to mental health services, etc.). To overcome this issue, members of several community SMD organizations and family associations will also be recruited.

## Conclusions

The results of this study may demonstrate the effectiveness of a novel NNP in optimizing treatment adherence and ensuring healing from HCV in this population.

## Data Availability

Not applicable.

## Abbreviations

SMD: Severe Mental Disorder
HIV: Human Immunodeficiency Virus
HBV: Hepatitis B virus
HCV: Hepatitis C virus
NNP: Nurse Navigator Program
LSP: Life Skill Profile
PANSS: Positive and Negative Syndrome Scale
ITT: Intention To Treat
